## Abstract

**Background:**

Lesbian, gay, bisexual, transgender, queer, and intersex (LGBTQI+) patients continue to experience stigma, discrimination, and inadequate knowledge among mental health and medical professionals. These barriers can negatively impact health care outcomes, leading to delayed treatment, mistrust, and unmet medical needs within LGBTQI+ communities. Providing culturally competent care to LGBTQI+ people remains a critical challenge within health and social care. The development and use of reliable and valid assessments examining LGBTQI+ health care professional competency continue to be important in understanding and ameliorating LGBTQI+ health inequalities.

**Objective:**

The aim of the study is to develop and psychometrically validate a new multinational instrument designed to assess health care professionals’ LGBTQI+ attitudes, awareness, general skills, and knowledge, as well as to examine LGBTQI+ workplace affirmative policies, support, and climate.

**Methods:**

An initial pool of 100 new scale items was developed by reviewing existing LGBTQI+ health care scales and consulting with LGBTQI+ health care experts in the summer of 2023. Leading experts in LGBTQI+ health care were then asked to participate in the Delphi method to provide numeric and qualitative feedback on the 100 items. This process yielded a final primary survey comprising 39 test items. A cross-sectional multicenter, multicountry scale validation study using a web-based survey was administered to health care professionals and trainees in Italy, the United States, and the United Kingdom between October 2024 and December 2025 using a convenience sampling approach complemented by snowball recruitment. Research participants were asked to complete a demographic and professional survey, the 39 new test items, the 18-item Lesbian, Gay, Bisexual, and Transgender Development of Clinical Skills Scale (LGBT-DOCSS), and the 12-item Workplace Support subscale of the LGBT Climate Inventory (LGBTCI).

**Results:**

Funding commenced in May 2023, and data collection was conducted from October 2024 to December 2025. A total of 1339 eligible people completed the survey. Data analysis has started, and results will be reported in theautumn of 2026. It is anticipated that the Professional Readiness in Diversity and Equity (PRIDE) scale will emerge as a reliable and valid tool for assessing health care professionals’ LGBTQI+ attitudes, awareness, general skills, and knowledge, as well as examining LGBTQI+ workplace affirmative policies, support, and climate. The instrument may also serve as a useful outcome measure in research evaluating professional practice and development.

**Conclusions:**

The development and validation of the new PRIDE scale represent a significant advancement toward improved cultural competence among health care professionals. Validating the scale in both English- and Italian-speaking populations will support the development of international interventions and, ultimately, treatment outcomes for LGBTQI+ people. The PRIDE scale has the potential to exert a far-reaching impact on the delivery of clinical care and public health services worldwide.

## Introduction

A growing number of adults now identify as lesbian, gay, bisexual, transgender, queer, and intersex (LGBTQI+), even as this increase coincides with a rapid and broadening backlash against LGBTQI+ communities [1,2]. Health and social care systems remain critically challenged in providing adequate care to these populations [3-7]. LGBTQI+ people report higher rates of stigma and discrimination, as well as inadequate health care professional knowledge during health care encounters, compared with heterosexual and cisgender peers, which in turn leads to mistrust, delayed treatment, and unmet medical needs in the LGBTQI+ community [8-11]. These patterns are observed in multiple nations and ultimately lead to extensive health inequities in these populations worldwide [1,5].

It is incumbent upon the health care system to address the drivers of these systemic inequities [12,13]. One such driver is the inconsistent and often inadequate care provided by individuals within the health care system [6,7,14,15]. Health care professionals should consistently provide competent and inclusive care to LGBTQI+ individuals. Such care is grounded in respect for LGBTQI+ identity, acknowledges the unique life experiences of LGBTQI+ individuals, and is aware of the population-level health inequities experienced by these communities [16-18]. However, continuing negative experiences of LGBTQI+ people in the health care system emphasize that many health care professionals fail to provide this standard of care.

The principles of quality assurance in health care dictate that improving the health care system requires being able to systematically monitor, evaluate, and elevate standards of care [19,20]. To address the well-documented health inequities experienced by LGBTQI+ patients, it is therefore essential to be able to measure and address health care professionals’ knowledge, clinical skills, and prejudice toward the LGBTQI+ community [21]. Numerous psychometric tools have been developed to evaluate health care professionals’ clinical preparedness and attitudes toward LGBTQI+ patients. These tools play an essential role in identifying gaps in knowledge, biases, and areas for improvement in delivering inclusive and competent care. For example, the Lesbian, Gay, Bisexual, and Transgender Development of Clinical Skills Scale (LGBT-DOCSS) [22] evaluates key areas of competence in health and social care, including clinical preparedness, attitudinal awareness, and knowledge. The QUeering Individual Relational and Knowledge Scales (QUIRKS) compare health care professional and patient experiences in the health care system [23], and the Lesbian, Gay, Bisexual, and Transgendered Climate Inventory (LGBTCI) assesses the perceived inclusiveness of health care environments [24].

Of the scales that specifically focus on health care professionals, the LGBT-DOCSS is the most widely used across a variety of health care contexts [21]. However, this and many other instruments no longer fully reflect contemporary language, concepts, or understandings of LGBTQI+ identities. Over time, the terminology and concepts used to describe sexual orientation, gender identity, and gender expression have changed significantly, and these changes need to be reflected in new LGBTQI+ assessment scales. Outdated scales can be stigmatizing for LGBTQI+ people as well as contribute to perpetuating inequalities through the generation of poor quality and reduced construct validity. In addition, there is now greater awareness that organizational climate and support for LGBTQI+ people play an important role in driving health care professionals’ attitudes and behaviors toward this population [25-27]. Considering the impact of the LGBT-DOCSS, we acknowledge the need to develop a new LGBTQI+ cultural competency scale that is multinational in its development and psychometric evaluation, reflects more contemporary language and conceptual nuance, and incorporates assessment of workplace climate.

The overarching aim of this study is to develop and validate a new multinational psychometric instrument that can assess health care professionals’ LGBTQI+ attitudes, awareness, general skills, and knowledge, as well as examine perceptions of LGBTQI+ workplace climate. Development of the new Professional Readiness in Diversity and Equity (PRIDE) scale addresses the continual evolution of language and cultural understanding surrounding LGBTQI+ identities and the emergence of new challenges faced by LGBTQI+ people within health and/or social care settings. The objectives of this protocol are to outline the methodological framework used to design and validate the PRIDE scale. We begin by discussing how we generated our sample and how we designed candidate items and measures. We describe in detail the analytic methods used to identify and validate the factor structure and to evaluate the psychometric properties of the scale. Finally, we address plans for validating the applicability of this scale across demographic groups and international or institutional contexts. The resulting instrument is intended to provide a robust, multidimensional assessment of clinical competence among health care professionals in diverse cultural and organizational settings.

## Methods

### Scale Development and Measures

The PRIDE Scale included 39 new test items examining LGBTQI+ health care knowledge, awareness, attitudes, skills, and the work environment,. Development of these items was iterative and generated through literature reviews, expert consultation, and adaptation from existing scales. The Delphi method was used to select the most relevant items via iterative rounds of feedback from an expert panel. The first step was to identify and recruit a diverse group of international experts with relevant experience in LGBTQI+ health care, psychometric scale development, and clinical competence. These experts included health professionals (mostly physicians and psychologists), LGBTQI+ health advocates, clinicians, researchers, public health professionals with expertise in biostatistics and epidemiology, and educators. In total, the panel was comprised of 12 members. There were 3 Delphi rounds. In the first round of item generation, experts on the study team developed a broad number of items (100) both from the existing literature and newly formed items, which were then randomly listed and presented to the expert panel. Experts were asked to evaluate each item based on its relevance, clarity, and its potential importance for measuring LGBTQI+ related competencies among health care professionals. Experts could also comment on each item and suggest new or adapted items. After the first round, responses were scored for relevance and ordered accordingly. Quantitative consensus was defined a priori as a threshold of ≥75% and a median rating of ≥4 on a 5-point scale indicating an item as important or very important. These thresholds align with accepted Delphi standards and ensure that retained items reflect high agreement and rating stability. Based on the scoring (1-100), 39 items that showed strong consensus for inclusion were retained. These items are measured on a 5-point Likert-style scale that ranges from 1 (strongly disagree) to 5 (strongly agree).

In designing the scale, the team made several decisions to ensure applicability and interpretability. We drew upon existing implicit bias scales. While the scale is aimed toward those who provide clinical care, we ensured that the questions had a broad reach by using “clients or patients” instead of “patients” alone. We also avoided questions that were overly technical or related to specific specializations. While we believe it is important to address the needs of specific sexual and gender minority groups, we restricted these to a few questions rather than repeating questions by group. We elected to phrase questions in a way that addresses perceptions of one’s specific institution rather than perception of self. Finally, we avoided some questions over concerns about long-term relevance (eg, specifying pronouns when working with colleagues or clients, as this may become more normalized over time).

In addition to the 100 test items, to enable convergent construct validity testing and criterion and concurrent validity testing of the PRIDE scale, 2 further scales were used forming part of the main survey; these included the LGBT-DOCSS [22]; and the LGBTCI [24,28]. The LGBT-DOCSS is an internationally established, interdisciplinary self-assessment for health and mental health professionals working with LGBT clients [21]. The scale is comprised of 18-items and 3 subscales (clinical preparedness, attitudes, and knowledge). Items are rated on a 7-point Likert scale (1 strongly disagree to 7 strongly agree), with 8 items reverse-scored. For our purposes, we adjusted this to a 5-point scale, as we felt it would reduce cognitive load and potentially improve response rates. The loss of granularity would have minimal to no loss of psychometric information. From these items, a total mean score and 3 subscale scores (clinical preparedness, attitudes, and knowledge) can be computed. Higher scores thus reflect greater levels of LGBT cultural competence. The LGBT-DOCSS has demonstrated strong reliability and construct validity [22]. The LGBTCI is a well-used and researched assessment of LGBT workplace support and overall climate [24,28]. For this survey, we used only the 12-item Workplace Support subscale, in which items are rated on a 4-point Likert scale from 1 (doesn’t describe at all) to 4 (describes extremely well).

Additionally to the above, the main survey also included screening items (namely, consent, previous participation check, and age) and demographics (current employment, clinical and practice specialization, health and social care facility type, gender identity, sexual orientation, network diversity, ethnicity, and political ideology). The exact items and their phrasing were adjusted between the United States and European versions of the surveys to ensure cultural relevance.

### Design

A cross-sectional multicenter, multicountry scale validation study. Participants were recruited from October 2024 to December 2025. Study sites were located in Boston (United States), Washington, DC (United States), New York (United States), Brighton (United Kingdom), and Verona (Italy).

### Study Population and Sample

The study population consisted of health professionals, including students or health professionals-in-training, such as physicians, nurses, and other allied health professionals (eg, podiatrists, occupational therapists, physiotherapists, and mental health professionals) working in Italy, the United Kingdom, and the United States, with respondents able to complete the survey in English or Italian, depending on the country. The goal was to have a norming sample of international health care professionals including those in-training.

Sample size was calculated considering the 2 main statistical techniques to be used in the analysis: exploratory factor analysis (EFA) and confirmatory factor analysis (CFA). Based on the literature, as a rule of thumb (item-to-participant ratio), 5 to 10 participants per item are required [29-32]. For the 39-item PRIDE scale, this would translate to a minimum of 195 participants (5 participants per item) and a preferred sample size of 390 participants (10 participants per item). However, as we are planning an EFA and CFA, a total of approximately 700 participants is planned. For test-retest reliability, based on Walter et al [33], and assuming a null intraclass correlation coefficient of 0.40, an expected intraclass correlation coefficient of 0.70, 2 administrations of the scale, a significance level (α) of 0.05, and a power (1–β) of 0.80, a sample size of 62 is required.

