#### Reliability Estimates and Test-Retest Reliability

Internal consistency reliability for the PRIDE scale will be evaluated within each sample (United States and Europe) and reported for each subscale, and for the total scale only if a defensible higher order or general-factor model supports total scoring. Reliability will be quantified using Cronbach α and, for ordinal Likert-type items, ordinal alpha (α_ord) computed from a polychoric correlation matrix. In addition, McDonald omega (ω) will be estimated for each monotone or unidimensional subscale using a congeneric factor model (allowing heterogeneous item loadings) and will be treated as the primary model-based estimate; where relevant, omega estimates derived under an ordinal framework (polychoric correlations or appropriate ordinal estimators) will be reported. Item-total correlations will be examined to assess the contribution of individual items to subscale reliability, and items with low item-total correlation (eg, <0.30) will be flagged for potential removal in conjunction with evidence from MSA, CFA (factor loadings or model fit), and IRT GRM outputs (discrimination, thresholds, and information), in accordance with the prespecified item selection rules. Test-retest reliability correlations will establish temporary (2-wk) stability of the PRIDE Scale using the blinded combined United States and European samples pooled. The test-retest sample size power calculation suggested an ideal sample size of 62 for this reliability test.

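### The test-retest sample size of 62 does not follow from its stated inputs, which give 33 (one-sided) or 41 (two-sided)

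*Protocol article*

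**What the plan says.** The section Study Population and Sample gives a complete set of inputs for the retest calculation, citing a published ICC sample-size method. The calculation is made "assuming a null intraclass correlation coefficient of 0.40, an expected intraclass correlation coefficient of 0.70, 2 administrations of the scale". The same sentence sets α at 0.05 and power at 0.80, without saying whether α is one- or two-sided. The result is given as "a sample size of 62 is required".

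The section Reliability Estimates and Test-Retest Reliability repeats the number: "The test-retest sample size power calculation suggested an ideal sample size of 62 for this reliability test". On the analysis itself, that section says: "Test-retest reliability correlations will establish temporary (2-wk) stability of the PRIDE Scale using the blinded combined United States and European samples pooled".

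Neither section states sidedness, and neither mentions an allowance for dropout between administrations or any other inflation.

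**The concern.** Everything the calculation needs is stated except sidedness, so a reader can repeat it, and it does not come out at 62 under either choice of sidedness. This is not detail left to a fuller plan: the inputs and the result are both printed, and they disagree.

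The null ICC is the benchmark that retest stability is meant to exceed. If 62 was computed from different inputs, a reader cannot tell whether that benchmark is 0.40 or some other value, and the stated power of 0.80 does not belong to the design as described.

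**Working it through.** **Inputs** (all from Study Population and Sample): null ICC ρ0 = 0.40; expected ICC ρ1 = 0.70; k = 2 administrations; α = 0.05, sidedness not stated, so both are tried; power 0.80.

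**Formula** (standard approximation for testing an ICC):

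n = 1 + 2(zα + zβ)² k / [(ln C0)² (k − 1)], with C0 = (1 + kθ0)/(1 + kθ1) and θ = ρ/(1 − ρ).

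**Attempt to reproduce 62**

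- θ0 = 0.40/0.60 = 0.667 and θ1 = 0.70/0.30 = 2.333
- C0 = (1 + 1.333)/(1 + 4.667) = 2.333/5.667 = 0.412
- (ln C0)² = (−0.887)² = 0.787
- One-sided: (1.645 + 0.842)² = 6.18, so n = 1 + 4 × 6.18/0.787 = 32.4, or 33
- Two-sided: (1.960 + 0.842)² = 7.85, so n = 1 + 4 × 7.85/0.787 = 40.9, or 41

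The figure of 62 is not reproduced.

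**Does another version of the same calculation reach 62?**

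| Method, null 0.40 vs 0.70 | One-sided | Two-sided |
|---|---|---|
| Approximation above, power 0.80 | 33 | 41 |
| Exact F test, power 0.80 | 33 | 42 |
| Fisher z (n − 3), power 0.80 | 35 | 43 |
| Approximation, power 0.90 | 45 | 55 |

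None does. Unstated attrition would have to be 1 − 33/62 = 47% (one-sided) or 1 − 41/62 = 34% (two-sided).

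**Power at n = 62.** The exact test compares an F ratio on n − 1 and n degrees of freedom with its critical value. Under ρ1 that critical value is scaled by C0.

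| Null ICC | One-sided α 0.05 | Two-sided α 0.05 |
|---|---|---|
| 0.40 (as stated) | 96% | 93% |
| 0.50 (not stated) | just under 80% | about 70% |

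**Where 62 might have come from.** Changing only the null to 0.50 gives θ0 = 1, C0 = 3/5.667 = 0.529 and (ln C0)² = 0.404. One-sided, n = 62.1; two-sided, n = 78.6, or 79. The one-sided value is close, but strict rounding up gives 63, and exact power at 62 is slightly below 0.80.

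Other departures also reach 62. With the null kept at 0.40 and a two-sided α of 0.01, exact power is 0.799 at 61 and 0.807 at 62, so 62 is the smallest adequate number. Adding 50% to the two-sided figure gives 41 × 1.5 = 61.5, or 62. The article states none of these.

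**The case against.** The best defence is that the discrepancy is harmless. If 0.40 is the intended null, 62 is conservative. If the null was really 0.50 and one-sided, power is about the planned 80%. Test-retest stability is one secondary property: the main sample is sized on the factor analyses, and the article makes the confirmatory factor analysis the primary evidence for the latent structure. Data collection ended in December 2025, so the figure no longer steers recruitment. All of this stands. It limits the severity, but it does not make the stated inputs yield the stated number.

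Three stronger readings are tempting and should be resisted.

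- **That the authors used a null of 0.50.** The match is close but needs one-sided α and rounding down, and it is not unique. It remains an inference.
- **That the retest is underpowered.** Among the cases considered here, a material shortfall at 62 arises only if the intended null was 0.50 and the test two-sided (about 70%). Nothing in the text points to that combination.
- **That the analysis plan contradicts the calculation.** The reliability section speaks of correlations on pooled US and European data, which a reader might take to mean Pearson coefficients that ignore a systematic retest shift and gain from between-country differences. The article never says Pearson, and the sample-size section frames test-retest as an ICC. Any amount of overstatement would rest on shifts and country differences that the article does not give. Pooling is also a defensible target, given the stated aim of an international norming sample. What remains is a request to name the statistic.

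**Conclusion.** The point holds as an arithmetic inconsistency. The stated inputs require 33 participants one-sided or 41 two-sided, against 62 printed in two sections. At 62, power against the stated null is about 96% or 93%, not 80%. This rests on the standard ICC formula and is confirmed by the exact F test; Fisher z lands within two participants of the formula. It also assumes that no inflation was applied, since none is stated.

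Which element is wrong (null, α, an omitted inflation, or N itself) cannot be settled from the article. The consequence is an unclear benchmark and a misdescribed power for a secondary reliability property. The inconsistency does not undermine the validation study.

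**What to change.** Reconcile the null ICC, α and its sidedness, power, any inflation and N, and make the two sections agree. There are two ways to do this:

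- Keep the null at 0.40, restate the required number as 33 (one-sided) or 41 (two-sided), and say that 62 gives power of about 96% or 93%.
- If a different input was actually used, print that input and the sidedness, and show that they lead to 62. For example, a null of 0.50 would have to be stated as one-sided; two-sided it calls for 79.

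In either case, state the null value with which the estimated ICC will be compared, and in Reliability Estimates and Test-Retest Reliability name the statistic as the ICC used in the calculation.

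The cost is a few words and one restated figure, with no new data and no extra participants. The article places the analysis in summer 2026, so the benchmark can be settled before results are reported.

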### Inclusion and Exclusion Criteria

Eligible participants needed to be aged 18 years or older and be a health care professional or health care educator in a health and/or social care setting in Italy, the United Kingdom, or the United States (eg, physician, psychiatrist, psychologist, counselor, social worker, occupational therapist, university lecturer, paramedic, nongovernmental organization practitioner, nurse, etc) or currently training for a profession involving health and/or social care (eg, student nurse, medical student, mental health therapist-in-training); and be able to provide informed consent (online) to participate in the survey. Exclusion criteria were those aged under 18 years, and not a health care professional (or educator) or health care professional (or educator) in-training.

